### Statistical analysis

The planned sample size is 200 pediatric subjects with influenza (134 in the baloxavir treatment group and 66 in the oseltamivir treatment group). Because of the anticipated challenges in enrolling patients during the COVID-19 pandemic and because the study is not designed to demonstrate noninferiority or superiority considering feasibility, no formal statistical sample-size calculations will be performed. The intention-to-treat infected population for efficacy will include all subjects who receive at least one dose of baloxavir or oseltamivir and who have a confirmed diagnosis of influenza virus infection by RT-PCR on Day 1. Based on our past experience in clinical studies in Japan [27, 28], it is expected that almost all subjects with a positive rapid influenza diagnostic test be confirmed for influenza by RT-PCR. The safety population will consist of all subjects who receive at least one dose of baloxavir or oseltamivir. Statistical analysis will be based on descriptive statistics and no statistical tests will be used.

For the primary endpoint, the median TTIA (95% confidence interval [CI]) will be assessed using Kaplan–Meier curves for each treatment group, and the efficacy of baloxavir compared with oseltamivir will be assessed using between-group differences (95% CI). As a secondary analysis, the restricted mean survival time (RMST) and 95% CI up to Day 9 will be estimated for each treatment group by direct integration of the Kaplan–Meier survival curve. The between-group difference in RMST (95% CI) will also be calculated. The secondary time-to-event efficacy analyses will be assessed in the same manner as the primary analysis for the primary endpoint. For all other analyses, quantitative data will be summarized by descriptive statistics (mean, standard deviation [SD], maximum, median, minimum) and the mean between-group difference (95% CI). Qualitative data will be summarized by frequency, proportion, and the between-group difference in proportion (95% CI) using the Santner and Snell method.

The number of participants with AEs, SAEs, AEs leading to discontinuation, and AEs possibly related to study drug, as well as the number of deaths, will be summarized for each treatment group, and AEs will be coded using the Medical Dictionary for Regulatory Activities. Incidence rates will be calculated as the proportion of participants in the analysis population, and 95% CI using the Clopper-Pearson method. The change in each vital sign from baseline (predose) will be calculated for each treatment group.

Data obtained outside the allowable ranges described in Table 2 will be treated as missing, and values will not be imputed at each visit. All analyses will be conducted using SAS® software, version 9.4 (SAS Institute Inc., Cary, NC, USA).

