## Background

Influenza virus infections commonly occur in children and can be associated with serious complications such as febrile seizures and influenza encephalopathy, and significant socioeconomic burden [1–4]. Globally, influenza infection is estimated to be responsible for 16% of hospitalizations for respiratory disease among children 5–17 years [3] and 5% of hospitalizations for acute lower respiratory disease among children < 5 years [5]. Similarly, in Japan, approximately 25% of influenza infections occur in children 6–12 years, and hospitalizations due to severe influenza-related complications are higher in children than adults and are highest in children < 5 years [6]. Preventing influenza infection in children is particularly important because they are a common source of influenza transmission among households and the wider community [7, 8]. While annual vaccination is the most effective means of preventing influenza and influenza-related complications [1], effectiveness is limited by the emergence of new influenza virus subtypes, the increased susceptibility of children to influenza infection, and decreased vaccine coverage and availability [9–11].

Neuraminidase inhibitors (NAIs) are recommended for the treatment of influenza virus infection in children who are critically ill or at high risk of complications, are symptomatic and have household members who are at high risk of developing influenza complications, and are within 2 days of symptom onset [1]. In children, NAIs have been shown to reduce the duration of influenza illness [12] and the incidence of influenza-associated acute otitis media [13], and may contribute to improved survival in those who are critically ill [14]. However, there may be differences in the effectiveness of NAIs across influenza types in young children (1–5 years) as shown by oseltamivir, which is less effective against influenza type B virus than influenza type A virus [15]. In addition to intrinsic factors such as age and immune status, other factors that may contribute to reduced effectiveness include nonadherence to a repeat-dose treatment regimen or difficulties with inhaled routes of administration [16, 17]. Further, emerging resistance to current NAIs indicates that new antiviral treatments with different mechanisms of action are needed to complement the currently available options for antiviral therapy [18, 19].

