Eligible subjects will be registered and randomly allocated (2:1) to the baloxavir and oseltamivir groups using an interactive web response system (Fig. 1). Randomization will be stratified using stochastic minimization to balance age (≥ 6 to < 9 years, ≥ 9 to < 12 years) and baseline total score for the Influenza Symptom Severity Scale for respiratory symptoms (cough and nasal discharge/nasal congestion) (≤ 3, ≥ 4). The Influenza Symptom Severity Scale is rated by subjects or with assistance from a parent/guardian on a 4-point scale (0 = no symptoms, 1 = mild, 2 = moderate, 3 = severe). All study drugs will be administered by the subjects themselves or with assistance from a parent/guardian.

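### Allocation is minimised on age and baseline respiratory score, but the RMST difference as worded is unadjusted, so its CI is wider than needed to the extent that those factors are prognostic

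*Protocol article*

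**What the plan says.** **Allocation (Protocol article, Trial design).** "Eligible subjects will be registered and randomly allocated (2:1) to the baloxavir and oseltamivir groups". "Randomization will be stratified using stochastic minimization to balance age" in two bands (6 to under 9 years, 9 to under 12 years). The second factor is the "baseline total score for the Influenza Symptom Severity Scale for respiratory symptoms", meaning cough plus nasal discharge/congestion, cut at 3 or less against 4 or more.

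**Analysis (Protocol article, Statistical analysis).** The primary comparison takes Kaplan–Meier medians by arm, and "the efficacy of baloxavir compared with oseltamivir will be assessed using between-group differences (95% CI"; no interval method is given. As a secondary analysis, RMST to Day 9 is obtained in each arm by integrating that arm's Kaplan–Meier curve. Then: "The between-group difference in RMST (95% CI) will also be calculated". Neither minimisation factor appears in the section.

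**Size and purpose.** The planned arms are "134 in the baloxavir treatment group and 66 in the oseltamivir treatment group". Because the size is set by feasibility, "no formal statistical sample-size calculations will be performed". The analysis is descriptive, with no statistical tests.

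**The concern.** Minimisation makes the arms more alike on age group and baseline score than simple randomisation would. If those factors predict the outcome, the true sampling variation of the treatment difference falls. A standard error computed from two separate, unadjusted Kaplan–Meier curves does not register this, because the spread due to the factors is still inside each curve. The interval is then wider than the design has earned.

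The score is a plausible predictor. It sums the same two symptoms that must both fall to absent or mild for the primary endpoint to be met.

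With no test, margin or power target, the comparison is carried by the estimates and their intervals, and the comparator arm has only 66 children. Precision already secured by the allocation is worth keeping.

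**Working it through.** **1. The plan's own figure.** 200 × 2/3 = 133.3 and 200/3 = 66.7, against 134 and 66 in the article. These agree to within one child per arm. There is no power or precision figure to reproduce.

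**2. Is the score plausibly prognostic?** Each symptom is rated 0 to 3, and entry requires at least one at 2 or 3. The possible pairs are:
- Total 3 or less: (2,0), (2,1), (3,0) and mirrors. Exactly one symptom has to improve.
- Total 4 or more: (2,2), (2,3), (3,3), (1,3) and mirrors. Both have to improve, or one severe symptom does.

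The cut therefore largely separates children with one symptom to clear from children with two. As an illustration, suppose two independent, identical exponential symptom times. Waiting for both multiplies the mean by 1.5 and the median by about 1.8, which is about 0.4 to 0.6 on the log-time scale. Correlation between symptoms, and the fever criterion that all children share, would reduce this. It shows plausibility and is not an estimate.

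**3. Inputs for the size.**
- From the article: n = 200, 2:1 allocation, two binary factors, and a median time of 45 h (the earlier Japanese paediatric studies cited in the Discussion).
- Assumed: Weibull times with shape 1.3, each factor level at 50%, the same hazard ratio for both factors, biased-coin minimisation, no treatment effect, no dropout, and Day 9 taken as τ = 216 h.

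**4. Formulas.**
- RMST in arm a is the integral of S_a(t) from 0 to τ, and D is the difference between arms.
- Unadjusted variance in an arm: the sum over event times of A_i² / [Y_i(Y_i − 1)], where A_i is the area under the curve from t_i to τ and Y_i is the number at risk. SE(D) is the square root of the two arms' variances added together.
- Stratified: D_s = Σ w_k D_k with variance Σ w_k² V_k, over the four age-by-score cells. Here w_k is the share of children in cell k.
- Excess width = mean SE(D) / true sampling SD of D − 1.

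**5. Results (1,500 trials per row; SE, SD and half-widths in hours).**

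| HR per factor | Unadjusted SE | Sampling SD | Excess | Coverage | 95% half-width, unadjusted / stratified | Stratified coverage |
|---|---|---|---|---|---|---|
| 1.0 | 6.27 | 6.34 | −1% | 94.8% | 12.3 / 12.1 | 94.4% |
| 1.25 | 6.36 | 6.41 | −1% | 94.3% | 12.5 / 12.1 | 93.3% |
| 1.5 | 6.67 | 6.53 | 2% | 95.2% | 13.1 / 12.4 | 94.0% |
| 2.0 | 7.30 | 6.56 | 11% | 96.3% | 14.3 / 12.8 | 94.8% |
| 3.0 | 8.46 | 6.85 | 23% | 98.1% | 16.6 / 13.3 | 94.7% |

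For example, at HR 2.0: 7.30 / 6.56 = 1.113.

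**6. Reading the table.**
- The Monte Carlo error of each sampling SD is about 1/√(2 × 1500) = 1.8%. The first two rows are therefore compatible with no excess. The 2% at HR 1.5 is small against that error, and its sign rests on the trend down the table and on theory.
- Under shape 1.3, log-time effects of 0.3 to 0.6 correspond to hazard ratios of exp(1.3 × 0.3) = 1.5 to exp(1.3 × 0.6) = 2.2. Each row gives both factors the same strength, so a weaker age effect would mean a smaller excess.
- With weak factors, part of the stratified interval's narrowness is slight undercoverage. At 50% prevalence an oseltamivir cell holds about 66/4 = 16.5 children.

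**The case against.** The strongest objection is that nothing here is an error. An unadjusted interval after minimisation is valid and, if anything, conservative. The study is descriptive, without margin or test, so no formal decision turns on a few per cent of width. RMST is a secondary analysis. The prognostic strength of a dichotomised score is unknown, and the endpoint also needs temperature to fall, which the score does not measure. Four-cell stratification can undercover. All of this stands. It limits the point to a gain in precision of uncertain size.

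It does not remove the point. For RMST the article names a specific unadjusted estimator, so this is a stated analysis choice and not a detail left to a longer document.

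A reader might infer two stronger points, and the documents support neither:
- *That the primary median comparison also ignores the factors.* The article gives no interval method for the median difference. The full protocol and SAP are not shown, so adjustment is unstated there and not ruled out. The calculation above does not cover the median.
- *That virus type should be a covariate too*, because the Background describes "oseltamivir, which is less effective against influenza type B virus than influenza type A virus". That sentence concerns children aged 1 to 5 years, whereas this trial enrols ages 6 to under 12. It also describes a treatment effect that differs by type, which a main-effect covariate does not address.

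**Conclusion.** The point holds in conditional form. Allocation uses age group and baseline respiratory score, and the RMST difference as worded uses neither. To the extent that the factors are prognostic, its 95% CI is conservative and wider than needed: negligibly at a hazard ratio of 1.25 or below per factor, by about 2% at 1.5 and by about 11% at 2.0.

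Those hazard ratios are assumed, because the documents report no prognostic effect for either factor. The figures also rest on the Weibull shape, equal factor strengths and 216 h horizon listed above. The mismatch and its direction are well supported; the size is only moderately so. An unconditional statement that the intervals are too wide would go beyond the evidence. The consequence is lost precision, not bias, and it is shown for RMST only.

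**What to change.** Prespecify a between-group RMST difference to Day 9, with 95% CI, from an RMST regression or pseudo-value model with treatment, age group and baseline respiratory score category as main effects. Main effects are preferable to the four age-by-score cells, given the slight undercoverage seen with small cells. Report the unadjusted difference alongside. For the median difference, state how the CI is obtained and whether it uses the minimisation factors.

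The cost is SAP wording and a little programming. Both factors are recorded before allocation, so no data collection changes. The wording should be fixed before outcome data by arm are examined.

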### Clinical and laboratory monitoring

Eligible subjects will undergo a confirmatory test for influenza A or B at the screening visit on Day 1. To be included in the primary analysis population, influenza virus infection will be confirmed by reverse transcription-polymerase chain reaction (RT-PCR). A full description of the visit and assessment schedule is provided in Table 2. The following outcome measures will be assessed by subjects or their parent/guardian and recorded in an ePRO diary from postdose Day 1 to postdose Day 9: influenza symptom severity and body temperature (axillary) using an electronic thermometer taken right before or at least 4 h after administration of acetaminohen, if relevant; the severity of seven influenza symptoms (cough, sore throat, headache, nasal discharge/nasal congestion, feverish or chills, muscle ache or joint pain, and fatigue) will be assessed by subjects ≥ 7 years who are deemed able to assess influenza symptoms themselves; the severity of two influenza symptoms (cough, nasal discharge/nasal congestion) will be assessed by a parent/guardian for subjects < 7 years and/or those ≥ 7 years who are considered by the investigators to not able to assess influenza symptoms themselves.

**Table 2 Tab2:** Visit and assessment schedule

Day	1		2 +1 day	3	4	5 -1 to +2 days	6	7	8	9	10 −1 to +4 days 4	Discontinuation +14 days
Visit	1^a^		2			3						
	Pre dose	Post dose										
Informed consent	X											
Inclusion/exclusion criteria	X											
Demographics, clinical characteristics, and medical history	X											
Enrollment and randomization	X											
Baloxavir administration		X										
Oseltamivir administration		X	X	X	X	X						
Diary (ePRO)												
Body temperature	X	X^a^	qid		bid							
Influenza symptom severity	X	X^a^	bid									
Medical examination^b^	X		X			X					X	X
Vital signs	X		X			X					X	X
Influenza RIDT	X^c^											
SARS-CoV-2 test	X^d^		X^e^									
Influenza virus tests (RT-PCR, titer, RNA, PA, or NA sequence)	X		X			X					X	X
Influenza virus serum antibody titer test (HI method)	X											
Intrahousehold influenza infection rate questionnaire											X	X
TEAE reporting	X	X	X	X	X	X	X	X	X	X	X	X

X denotes assessment to be undertaken

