Virological endpoints Infectious influenza virus titer and the amount of virus RNA (determined by RT-PCR) at each time point Change from baseline in infectious influenza virus titer and amount of virus RNA (determined by RT-PCR) at each time point Proportion of participants whose influenza virus titer and quantitative RT-PCR are above and below the lower limits of quantification at each time point Time to the first cessation of viral shedding based on the influenza virus titer, defined as the time postdose until virus titers reach the lower limit of quantification for the first time Time to sustained cessation of viral shedding based on influenza virus titer, defined as the time from the last positive virus titer postdose to the first virus titer that is below the lower limit of quantification	
Exploratory endpoints	
Emergence of amino-acid substitutions (PA/I38X and NA/H275Y) in subjects who are RT-PCR positive for influenza infection pre- and postdose. Treatment-emergent influenza virus substitutions in PA/I38 or NA/H275 will be defined as amino-acid substitution occurring between Day 1 and the last time point where the influenza virus RT-PCR cycle threshold is < 31 for the H1 subtype or < 29 for the H3 subtype Rate of intrahousehold influenza infection	
Safety	
AEs, AEs possibly related to baloxavir or oseltamivir, SAEs, vital signs	

*AE* adverse event; *NA* neuraminidase; *PA* polymerase acidic protein; *RT-PCR* reverse transcription-polymerase chain reaction; *SAE* serious adverse event

The main secondary endpoints include the time to sustained resolution of influenza symptoms (cough, nasal discharge/nasal congestion, and body temperature) for at least 72 h; the time to resolution of fever (normal body temperature < 37.5 °C) for at least 12 h; the time to sustained resolution of fever for at least 72 h; the proportion of subjects with resolution of fever at each time point; the time to resolution of seven influenza symptoms (cough, sore throat, headache, nasal discharge/nasal congestion, feverish or chills, muscle ache or joint pain, and fatigue) for at least 21.5 h; the incidence of influenza-related complications and those influenza-related complications seen particularly in children (influenza-associated encephalitis or encephalopathy, febrile seizures, myositis); the use of antibiotics for treatment of infectious disease secondary to influenza infection; and the change from baseline in infectious influenza virus titer.

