## Discussion

MiniSTONE-2 was the first double-blind, randomized, active-controlled trial that was specifically designed to compare the efficacy and safety of baloxavir with oseltamivir in children aged 1 to < 12 years [24]. In that study, the median time (95% CI) to alleviation of influenza symptoms was similar between the treatment groups (baloxavir: 138.1 [116.6–163.2] hours versus oseltamivir: 150.0 [115.0–165.7] hours). In addition, and similar to the findings in adolescents and adults [22, 23], the reduction in viral load was faster with baloxavir compared with oseltamivir, with the median time to cessation of viral shedding shortened by approximately 24 h with baloxavir [24]. Consistent with the findings from studies in otherwise healthy adolescents and adults and those at high risk of influenza-associated complications, baloxavir was well tolerated with no unexpected AEs reported [22, 23], and the most frequently reported AEs were gastrointestinal (vomiting/diarrhea) in both treatment groups [24]. Although miniSTONE-2 was the first randomized active-controlled trial of baloxavir in children, this study was conducted in a non-Japanese population and included baloxavir 2% granules for oral suspension rather than tablets. In addition, in miniSTONE-2, baloxavir was administered at a different dose than is approved for use in Japan, but baloxavir exposure in miniSTONE-2 study is expected to be similar to that of Japanese individuals who are administered the Japanese approved dosage [25, 26].

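### Ordinary Kaplan-Meier medians are fixed for two viral-cessation times observed only at swabs around Days 2, 5 and 10, so the estimated difference in hours depends on the visit grid

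*Protocol article*

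**What the plan says.** Table 3 of the protocol article lists two cessation times based on infectious titer among the secondary endpoints. The first is "defined as the time postdose until virus titers reach the lower limit of quantification for the first time". The second, sustained cessation, is "defined as the time from the last positive virus titer postdose to the first virus titer that is below the lower limit of quantification".

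In Table 2, the row that begins "Influenza virus tests (RT-PCR, titer, RNA, PA, or NA sequence" is marked before dosing on Day 1 and after dosing only at Day 2 (+1 day), Day 5 (-1 to +2 days), Day 10 (-1 to +4 days) and at discontinuation.

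Under Statistical analysis, the median of the primary endpoint "will be assessed using Kaplan–Meier curves for each treatment group, and the efficacy of baloxavir compared with oseltamivir will be assessed using between-group differences", with 95% confidence intervals. The next step extends this: "The secondary time-to-event efficacy analyses will be assessed in the same manner as the primary analysis for the primary endpoint". Interval censoring is not mentioned, and virology is not excepted. Table 3 also plans the proportion of children above and below the lower limit of quantification (LLOQ) at each time point.

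**The concern.** The stated method suits the endpoint for which it was written. Time to illness alleviation is built from diary entries two to four times a day, so treating the recorded time as the event time costs a few hours at most. Time to cessation of shedding is built from three scheduled swabs. With ordinary Kaplan-Meier, a child whose titer is positive on Day 2 and negative on Day 5 becomes an event on Day 5, whenever in those three days shedding stopped. Each arm's median then moves to a swab date, and the difference between arms reflects where the medians lie relative to the swabs as much as the drug effect.

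The Discussion reports from the earlier pediatric trial "the median time to cessation of viral shedding shortened by approximately" 24 h. Readers will compare this trial's figure in hours with that one. The trial is descriptive, so the estimate and its interval are the whole result for these endpoints.

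**Working it through.** **Inputs from the article.** 134 baloxavir and 66 oseltamivir subjects. Taking Day d as (d - 1) x 24 h after dosing:

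- Day 2: nominal 24 h, window about 24 to 48 h.
- Day 5: nominal 96 h, window about 72 to 144 h.
- Day 10: nominal 216 h, window about 192 to 312 h.
- Nominal gaps: 96 - 24 = 72 h and 216 - 96 = 120 h.

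**Assumptions.** The article gives no absolute medians and no expected effect for this trial. The true difference is set at 24 h, the size it reports from the earlier trial. The true baloxavir median m is varied, and the oseltamivir median is m + 24.

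**Step 1: arithmetic on the nominal grid.** Let R(m) be the first nominal swab at or after m. The Kaplan-Meier difference then reads R(m + 24) - R(m).

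- 0 < m ≤ 24: 96 - 24 = 72 h (for example 12 v 36 h).
- 24 < m ≤ 72: 96 - 96 = 0 h (for example 48 v 72 h).
- 72 < m ≤ 96: 216 - 96 = 120 h (for example 84 v 108 h).

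On this grid, a true 24 h difference never reads as 24 h.

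**Step 2: simulation with visit variation.** Lognormal cessation times (SD of log 0.8), 134 v 66, 1,000 trials per cell, event dated at the first negative swab. Each entry is the median Kaplan-Meier difference in hours; the truth is 24 in every row.

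| True medians (h) | Nominal visits | Mostly nominal, some day shifts | Windows used evenly |
|---|---|---|---|
| 24 v 48 | 72 | 47 | 54 |
| 36 v 60 | 0 | 4 | 42 |
| 48 v 72 | 0 | 4 | 23 |
| 60 v 84 | 0 | 21 | 18 |
| 72 v 96 | 0 | 42 | 15 |
| 84 v 108 | 120 | 81 | 60 |

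The first entry, 24 v 48 h with nominal visits, is close to a coin toss: 47% of trials read zero and 53% read over 48 h.

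A further set of runs took baloxavir medians of 20 to 84 h and reported averages across trials: about 0 to 90 h with nominal visits, 9 to 59 h with visits mixed across days plus clock-time variation, and 19 to 49 h with windows used evenly.

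**Step 3: the same swabs, analysed as interval-censored.** A child with last positive swab at L and first negative swab at U contributes F(U) - F(L) to the likelihood; a child never negative contributes 1 - F(L). With a Weibull F, the difference in medians averaged 23 to 26 h under all visit patterns for medians of 20 to 84 h, including on lognormal data (SD about 5 to 14 h). In a separate Weibull run out to 96 v 120 h, the average fell no lower than 21.7 h. The 5 to 95% range widened from about 18-30 h for early medians to about 4-45 h for late ones.

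**Step 4: the second endpoint as worded.** Sustained cessation runs from the last positive postdose swab to the first negative one. Read literally, that is the gap between visits, nominally 72 or 120 h, and not a time since dosing.

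**The case against.** The strongest reply is that little hangs on this. The trial is descriptive, without tests or a sample-size calculation. The article's list of main secondary endpoints omits both cessation times and names change from baseline in titer instead. Titers and proportions below the LLOQ at each visit, which need no event time, are already planned. All of this stands and limits the weight of the point. It does not make the stated estimator suitable.

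A second reply is that an unseen analysis plan may specify interval censoring. It may, but the article does more than stay silent: it fixes the method for these endpoints.

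A reader might also infer stronger claims that the documents do not support:

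- *That the analysis cannot recover a 24 h effect.* It sometimes does. With windows used evenly, 48 v 72 h averages about 23 h.
- *That the result will be exactly zero.* Exact zeros need visits at nearly nominal times, and dosing clock time varies. With windows used evenly, readings within 6 h of zero are uncommon.
- *That the out-of-window rule, "Data obtained outside the allowable ranges described in Table 2 will be treated as missing, and values will not be imputed at each visit", discards useful titers.* The windows cover Days 2-3, 4-7 and 9-14. Only Day 8 and days after Day 14 fall outside them, and the discontinuation swab has its own window.
- *That children with no quantifiable baseline titer are counted as ceasing at their first swab.* The efficacy population requires only RT-PCR confirmation, so such children can be in it. The article does not say how the cessation analyses treat them.

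**Conclusion.** The point holds for the two viral-cessation endpoints only. The article applies a method for near-continuous diary data to events known only to lie between widely spaced swabs, and the resulting difference in hours depends on the visit grid. For the same true 24 h, the average reading can lie anywhere from about 0 to 90 h under nominal visits. The range narrows to 19 to 49 h if the windows are used evenly. Where this trial would fall is unknown, because the true medians and the visit pattern are assumptions. The 24 h is an earlier trial's reported result, used here as a yardstick; its swab schedule and estimator are not given. Readings above and below the truth both occur, so the distortion favours neither drug consistently. The plan should be changed here, but the primary endpoint and the diary-based conclusions do not depend on it.

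**What to change.** Exempt both cessation endpoints from the sentence that carries the primary analysis over. Analyse them as interval-censored between the actual times of the last positive and first negative swab, for example with a parametric accelerated failure time model for the difference in medians and Turnbull curves for display. Count time from dosing for both endpoints, which means restating the definition of sustained cessation. Restrict both to children with a quantifiable baseline titer, since the others have no shedding to cease. If a Kaplan-Meier difference in hours is still shown, read it only alongside the already planned proportion below the LLOQ at each visit.

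The cost is analysis-plan wording and a standard procedure; no extra swabs, visits or children are needed. The downside is a parametric shape for the median. The Weibull fit tolerated lognormal data in the check above, but precision is modest when the medians are late.
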